### **5.2 Baseline Patient Characteristics**

The analysis sets are the Phase 1b trial set and the Phase 2a trial set.

Baseline patient-level demographic characteristics to be described are gender, ethnicity and age (age to be derived from the date of entry to trial – year of entry to trial- year of birth). Gender and ethnicity will be reported as number and percentage of the trial set and age will be reported as median, Interquartile Range (IQR), Range of the trial set. Please see Appendix 2 for dummy table for baseline characteristics.

Clinical characteristics regarding medical history and concomitant medications will be categorised and tabulated at the patient-level. Tumour location (%) and appearance (hairy or non-hairy) at entry will be reported by randomised group in the Phase 2a trial set at the tumour-level.

## **6. TREATMENT RECEIVED**

Phase 1b will be open label and Phase 2a will be a randomised double blind trial.

In both Phases the dose will be one application in the evening to each tumour as directed at the first visit by the research nurse/doctor. Application will be recorded in a patient diary.

In Phase 1b the participant's will treat their selected tumour with the active treatment for a 4 week period. In Phase 2a all participants will be treating tumours on one half of the body with active CT327 and the other half of the body with placebo according to the randomisation allocation for a 12 week period.

Withdrawals from treatment are cases where the trial drug is discontinued. This may be because the participant decides they no longer wish to continue, cessation of the trial drug is

recommended by the investigator, the participant is pregnant, there is a significant medical condition or an adverse localised or systemic reaction. In both cohorts, participants who withdraw from trial drug prior to the end of treatment visit, will be followed up and included in the analysis, if they are happy to do so.

The analysis sets are the Phase 1b treatment set and the Phase 2a treatment set.

Compliance to the treatment will be reported (Appendix 2) at the patient level as the percentage compliance in terms of days of missed ointment for all tumours. If additionally individual tumours have had missed treatment this will be reported at the tumour level as the number of missed applications (in days) as reported in the diary cards. The total number of applications, at the tumour-level, will be also be reported as median days (IQR, range), over 4 weeks in Phase 1b and over 12 weeks in Phase 2a.

The expected number of applications in a 4-week (28 day) period is 28 and in a 12 week (84 day) period is 84 (+/-3 days dependent on EoT visit date). Compliance to treatment will be summarised as the number of days on treatment (date end-date start) as recorded in the patient diary and reported as median (IQR, Range), as well as the proportion of protocol treatment received, calculated as the number of days of applications as a proportion of the 28/84 day protocol treatment, and reported with 95% Confidence Interval (CI).

The number of patients and reasons for non-compliance will be measured using the patient diaries. The median and IQR of the number of days where ointment was not applied will be reported and any necessary descriptions of the reasons for non-compliance as documented in the comments section of the patient diaries will be reported.

Drop-out of treatment due to pregnancy will be reported.

No significance testing will be carried out.

## **7. SAFETY ANALYSIS**

Most adverse events (AE) and adverse drug reactions that occur in this trial, whether they are serious or not, will be expected treatment-related toxicities due to the drugs used in this trial. For a full list of expected undesirable effects of CT327, please refer to the Investigator Brochure.

AE's are recorded by the clinical staff directly to the database on a three-point scale of severity (mild, moderate or severe) and also by causality (relationship to treatment categorised on a six point scale), as described in the protocol.

The analysis sets are the Phase 1b treatment set and the Phase 2a treatment set.

Any adverse events/reactions from start of treatment and up to the time of tumour excision (Phase 1b) or 4 weeks after end of treatment (Phase 2a), will be categorised according to severity and causality and recorded on the database.

The number of patients (Phase 1b) and tumours (Phase 2a) reporting any AE will be reported clarifying those deemed to be treatment related (Appendix 2).

In Phase 2a, the number of tumours with at least one AE will be reported as a proportion of the total number of tumours. The number of tumours with at least one treatment-related AE, that is those described as definitely, probably or possibly related, will be reported as a proportion of the total number of tumours. The number of tumours with at least one 'moderate' or 'severe' treatment-related AE will be reported as a proportion of the total number of tumours.

The unique number of patients experiencing at least one 'moderate' or 'severe' treatment-related AE will be reported as a proportion of the treatment set.

Proportions will be presented as % (95% CI).

Descriptions of the adverse events may require listing in the text.

No significance testing will be carried out.

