| Primary outcome:       | The proportion of tumours responding to treatment by 12 weeks.                                                                                                                                                                                                                                                                                                                                                                                                                                                                                                                                                                                                                                                                                                                                                                                                                                   |
| Secondary outcomes:    | 

a. Change in tumour volume from baseline (pre-randomisation) to 12 weeks

b. Adverse events within a planned 12-week treatment period

c. Compliance including reasons for non-compliance

d. Confirmation of the definition of response (currently according to WHO RECIST criteria where response is defined as >30% reduction in tumour volume, this will be used as a benchmark).

e. Expression of targets of TRK signalling in tumour biopsies as determined by QPCR and immunohistochemistry.

f. Patient reported quality of life using patient reported QoL tools (EQ5D, DLQI)

g. Assessment of acceptability of trial treatment according to patient treatment questionnaire (Appendix B).

h. Patient reported pain using the Patient Pain Assessment Form at 0, 4 and 12 weeks.

 |

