## 7.2 Cohort 2 summary

This is a phase 2a randomised, double-blind, single site, placebo controlled trial to investigate if CYLD defective tumours respond to CT327.

150 tumours will be needed to complete the trial, and recruitment will continue until we have the 12 week assessment for 150 tumours. We anticipate 15-20 patients may need to be recruited to the trial to achieve this.

Patients will typically have 8 or 10 eligible tumours each (see section 9.3 for cohort 2 inclusion criteria below).

Patients will be allocated both active and placebo treatments to be applied randomly to tumours on their left or right side (Group1: L=active; R=placebo, Group 2: L=placebo; R=active).

Four or five tumours on each side will be identified at baseline for measurements during the 12-week treatment period.

Photographs will be taken and the tumours numbered clearly and offered to the patients, who can refer to the tumour maps. They will be shown how to apply treatments using disposable finger tip applicators to prevent crossover and given a detailed instruction sheet for reference.

Volume measurements will be taken at baseline, week 4 and 12 at scheduled visits. All tumours will be assessed for tumour volume using the Life-Viz stereoscopic imaging system by a blinded assessor (Skvara, Kalthoff *et al.* 2011).

Patients will record application of treatment in a patient diary (See Appendix C).

Patients will also record if any of the selected tumours have any associated pain, this will be captured using the Patient Pain Assessment Form, which will be completed at baseline and repeated at 4 and 12 weeks.

After 12 weeks one tumour that is treated with active treatment and one tumour that has been treated with placebo will be biopsied to assess histological and immunohistochemical changes.

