### ***Telephone call (4 week follow up)***

Participants will be contacted by telephone 4 weeks after completing the trial to ensure there have been no further significant adverse events during this period. They will be asked if they have experienced any treatment site reactions since stopping treatment, or any other side effects. If necessary an appointment will be made for the participant to have a follow up visit in clinic for assessment and management.

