## **13.5 Tumour Biopsies**

**Cohort 1:** At the end of treatment visit, week 4, the routinely excised tumour will undergo routine analysis and some of the sample will be snap frozen and stored. This sample will be stored with a view to developing a CT327 skin assay. Participants will have the option to consent to samples potentially being used in future studies relating to the title of this trial.

**Cohort 2:** At the end of treatment visit, week 12, one tumour that has been treated with active treatment and one tumour that has been treated with placebo will be biopsied to assess histological and immunohistochemical changes. A proportion of these samples will be stored with the potential to undergo CT327 analysis in the future.

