## 17. Pharmacovigilance

### 17.1 Definitions

**Adverse event (AE):** Any untoward medical occurrence in a subject to whom a medicinal product has been administered, including occurrences which are not necessarily caused by or related to that product. An AE, therefore, does not necessarily have a causal relationship with the treatment. In this context, “treatment” includes all investigational agents (including comparative agents) administered during the course of the trial. Medical conditions/diseases present before starting trial treatment are only considered adverse events if they worsen after starting trial treatment.

**Adverse Reaction (AR)/Adverse Drug Reaction (ADR):** Any untoward and unintended responses to an Investigational Medicinal Product (IMP) which related to any dose administered to that subject. All AEs judged by either the reporting investigator or the sponsor as having reasonable causal relationship to a medicinal product qualify as adverse reactions. The expression “reasonable causal relationship” means to convey in general that there is evidence or argument to suggest a causal relationship.

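### The SAP's Phase 2a any-AE rate runs past the protocol's 12-week window and can include biopsy-site events; the table should be split at the biopsy

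*Combined protocol and SAP*

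**What the plan says.** **Window.** SAP section 7 collects adverse events from the start of treatment "up to the time of tumour excision (Phase 1b) or 4 weeks after end of treatment (Phase 2a". The protocol's Cohort 2 secondary outcome (section 4.2, repeated in the outcome table under 7.2) is narrower: "Adverse events within a planned 12-week treatment period".

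**Unit and measures.** In Phase 2a, SAP section 7 says "the number of tumours with at least one AE will be reported as a proportion of the total number of tumours". It then adds three proportions restricted by causality. The first begins "The number of tumours with at least one treatment-related AE, that is those described as definitely, probably or possibly related"; the other two are the moderate or severe related events, counted once by tumour and once by patient. The Appendix 2 safety table shows any AE by arm, with severity and relatedness rows hanging from it.

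**Definition.** Protocol 17.1 defines an AE as any untoward occurrence, "including occurrences which are not necessarily caused by or related to that product".

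**Biopsy.** Protocol 13.5 places the procedure at the week 12 end-of-treatment visit: "one tumour that has been treated with active treatment and one tumour that has been treated with placebo will be biopsied". The week 12 visit list in 13.4 and the schedule in 13.8 agree. The secondary objectives in 6.2 describe these two tumours as excised.

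**Collection afterwards.** The schedule in 13.8 marks AEs at a telephone call 4 weeks after the week 12 visit. The description of that call says: "They will be asked if they have experienced any treatment site reactions since stopping treatment, or any other side effects".

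**The concern.** Two features combine. First, the SAP window is longer than the protocol outcome, and the SAP plans no table for the 12-week outcome on its own. Second, the added weeks begin with a wound at one tumour per arm in each patient. Pain, bleeding or infection at that site meets the protocol's AE definition and is located at a treated tumour, so under the SAP rule the tumour counts as having had an AE.

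For Phase 1b the same SAP sentence ends the window at excision, and the protocol has surgery follow the completed treatment assessment. The Phase 2a window has no matching cut. The SAE exclusions in protocol 17.3 do not name the biopsy and do not apply to non-serious events. The Appendix 2 table has no biopsy row and no time split.

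What is at stake is how the descriptive safety table reads. No significance testing is planned, so readers will rely on the absolute rates and their 95% confidence intervals.

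**Working it through.** **1. The plan's own figure and the denominator.** Protocol 14.2 gives 75 tumours per arm, a null response rate of 5%, a target of 15%, and errors of 3.4% and 10.8%. Exact binomial calculation with a critical number of 8 gives P(X ≥ 8 | 75, 0.05) = 0.0336 and P(X ≤ 7 | 75, 0.15) = 0.1082, which match. The critical number is not printed in either document; 8 is the value between 6 and 10 that fits. This calculation is not in dispute. It only confirms 75 per arm as the working denominator.

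**2. Share of tumours biopsied per arm, f.** One tumour per arm per patient, with 15 to 20 patients:
- 15 patients: 15/75 = 20.0%
- 20 patients: 20/75 = 26.7%

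Within a patient the share is 1 in 5 (20%) or 1 in 4 (25%). The 26.7% arises only if 20 patients supply 75 tumours per arm, an average of 75/20 = 3.75 per side. With four per side throughout it is 20/80 = 25%.

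**3. Effect on the any-AE rate.** Let b be the risk of any other AE at a tumour and q the risk of a recorded biopsy-site event at a biopsied tumour. With the two independent,

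rate = b + f × q × (1 − b).

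The addition is at most f × q. For q = 10% that is 0.200 × 0.10 = 2.0 points or 0.267 × 0.10 = 2.7 points.

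The documents do not give q, so it is shown as a range. For illustration b = 3%, borrowed from the application site reaction figure in protocol 17.2. That figure comes from earlier studies and is not a per-tumour rate in this trial.

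| q (assumed) | 15 patients | 20 patients |
|---|---|---|
| 5% | 4.0% | 4.3% |
| 10% | 4.9% | 5.6% |
| 25% | 7.85% | 9.5% |
| 50% | 12.7% | 15.9% |

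If counting stops at the biopsy, every cell returns to 3%.

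**4. Effect on the contrast between arms.** Take true rates of 6% on active and 3% on placebo, 20 patients and q = 25%, so f × q = 0.0667.
- Active: 0.06 + 0.0667 × 0.94 = 12.3%
- Placebo: 0.03 + 0.0667 × 0.97 = 9.5%
- Difference: 3.0 points becomes 2.8
- Ratio: 2.0 becomes 1.3

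**5. Effect on the treatment-related proportions.** Let m be the share of biopsy events graded at least possibly related, so the rate is 0.03 + f × q × m × 0.97. With 20 patients and q = 25%, m = 0 leaves 3.0%, m = 10% gives 3.6% and m = 50% gives 6.2%. Nothing in the documents fixes m.

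**The case against.** A reader might infer that biopsy wounds contaminate the ointment's adverse event rates as a whole, or that they hide a real excess on active treatment. The documents do not support either reading.

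- **Causality grading handles much of it.** Three of the four proportions in SAP section 7 are restricted to treatment-related events, and Appendix 2 has a row for events that are not related. Protocol 17.1 defines the unlikely grade partly by another reasonable explanation, which fits a wound at a fresh biopsy site. The any-AE rate is by definition not a rate of harm from the ointment. This stands, with one limit: the possible grade allows for other contributing factors, so some biopsy events could be placed there.
- **The biopsies are balanced.** One tumour per arm is biopsied, so neither arm gains and the risk difference barely moves. Only the ratio falls noticeably, and the SAP plans no AE ratio. This stands.
- **Recording is uncertain.** Protocol 17.3 speaks of non-serious reactions recorded at trial visits, and 17.4 of non-serious events during drug treatment. Taken literally, minor events after the biopsy might never reach the database. The schedule in 13.8, the telephone call and SAP section 7 point the other way. This stands as a reason for caution about size, and is itself a conflict to resolve.
- **No decision depends on this rate.** SAP 8.4 rests predominantly on response. This stands.
- **Following patients after treatment is sensible.** It is, and the follow-up should be kept. The difficulty is merging it with the protocol outcome in one count.

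**Conclusion.** The point holds for the any-AE proportion and the severity rows that hang from it. As written, these can include biopsy-site events in 15 to 20 of about 75 tumours per arm (20% to 27%), and they answer a different question from the protocol's 12-week outcome. The mismatch of windows is a matter of text and needs no assumption.

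The numerical size does rest on assumptions: up to about 2 to 2.7 points per arm for each 10 points of biopsy-site event risk, if such events are recorded and each patient has both biopsies. The biopsy-site risk itself is not in the documents.

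The treatment-related proportions are affected only through events graded at least possibly related. There is no bias towards either arm and no effect on the primary outcome. This is a worthwhile, inexpensive improvement to a descriptive table, not a flaw in the trial's main conclusion.

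**What to change.** 1. In SAP section 7 and the Appendix 2 safety table, make the main tumour-level AE table cover start of treatment to the week 12 visit before biopsy. That is the protocol outcome.
2. Report events from the biopsy to the 4-week call in a separate table or row, by arm, with biopsied tumours identified. State how an event first noted on the biopsy day at a biopsied tumour is assigned.
3. Reconcile the AE recording windows in protocol 17.3 and 17.4, the 4-week telephone call in 13.4 and SAP section 7, so that it is clear whether non-serious events after treatment are recorded.

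This changes analysis wording for events the schedule already collects. Tumour-level counting already requires each event to be tied to a tumour, and the collection points (week 4, week 12, call) give the time split. No new visit or form field is needed, and no follow-up is lost. The downside is one extra table or row with small counts.

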## **17.2 Expected adverse reactions:**

Most adverse events and adverse drug reactions that occur in this trial, whether they are serious or not, will be expected treatment-related toxicities due to the drugs used in this trial. For a full list of expected undesirable effects of CT327, please refer to the Investigator Brochure.

The dose of CT327 to be used in this trial 0.5% as well as a dose of 0.05% have been used previously and were well tolerated by patients. In total 322 patients and 36 healthy volunteers have previously been treated with CT327 ointment and creams. The negative events that have been reported in previous studies include:

|          |    |
|----------|----|
| Pruritus | 6% |
| Eczema   | 6% |

|                                   |    |
|-----------------------------------|----|
| Headache                          | 5% |
| Nasopharyngitis                   | 3% |
| Diarrhoea                         | 3% |
| Application site pruritus         | 3% |
| Application site reactions        | 3% |
| Rhinitis                          | 2% |
| Upper respiratory tract infection | 2% |
| Cough                             | 2% |
| Back Pain                         | 2% |
| Dermatitis atopic                 | 2% |
| Dermatitis                        | 1% |
| Rash                              | 1% |
| Psoriasis                         | 1% |
| Fatigue                           | 1% |
| Vomiting                          | 1% |

CT327 has not been detected in the blood of any subjects treated with CT327 cream or ointment.

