#### 3. Overall, how satisfied were you with study medication?

- | Very satisfied           | Satisfied                | Neither
satisfied or
dissatisfied | Dissatisfied             | Very
dissatisfied     |
|--------------------------|--------------------------|-----------------------------------------|--------------------------|--------------------------|
|  |  |                 |  |  |

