### 3.2 Randomisation: Phase 2a only

Randomisation is at the per patient level randomising active and placebo treatments to left or right sided application. There are no stratification factors.

Four or five tumours matched for size will be selected on each side of the patient. Each tumour will be assigned a number to facilitate assessments and then each side of the patient will be allocated randomly to receive either active ointment or placebo ointment.

The number of tumours and unique number of patients recruited will be reported. The number of tumours in each of active and placebo group will be reported.

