**Secondary outcomes****Patient treatment Questionnaire**

|                                                                        | ACTIVE |                | PLACEBO |                |
|------------------------------------------------------------------------|---------------|----------------|----------------|----------------|
|                                                                        | Obs    | Percent | Obs     | Percent |
| How did you find the application of the ointment?               |               |                |                |                |
| Easy                                                                   |               |                |                |                |
| Neither easy or difficult                                              |               |                |                |                |
| Difficult                                                              |               |                |                |                |
| How long did it take to apply study treatment?                  |               |                |                |                |
| Less than 1 minute                                                     |               |                |                |                |
| More than 1 minute but less than 5 minutes                             |               |                |                |                |
| More than 5 minutes but less than 10 minutes                           |               |                |                |                |
| More than 10 minutes                                                   |               |                |                |                |
| Overall, how satisfied were you with the study medication?      |               |                |                |                |
| Very satisfied                                                         |               |                |                |                |
| Satisfied                                                              |               |                |                |                |
| Neither satisfied or dissatisfied                                      |               |                |                |                |
| Dissatisfied                                                           |               |                |                |                |

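### Phase 2a adverse events are summarised per tumour and arm, so most systemic events have no valid denominator; separately, the questionnaire shell contradicts the SAP text

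*Combined protocol and SAP*

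**What the plan says.** **Design.** SAP section 6 states that "all participants will be treating tumours on one half of the body with active CT327 and the other half of the body with placebo". SAP section 3.2 states: "Randomisation is at the per patient level randomising active and placebo treatments to left or right sided application". There is no active-only or placebo-only patient.

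**Adverse events.** For Phase 2a, SAP section 7 says that "the number of tumours with at least one AE will be reported as a proportion of the total number of tumours". It uses the same unit for related events ("The number of tumours with at least one treatment-related AE") and for moderate or severe related events, and it asks for 95% confidence intervals. One line is at patient level. It begins "The unique number of patients experiencing at least one" and covers moderate or severe treatment-related AEs only. Listing event descriptions in the text is left optional. The AE shell in SAP Appendix 2 has a single block of tumour rows under Active, Placebo and Total, with no patient rows. Protocol section 14.1 (cohort 2) also speaks of proportions of tumours with AEs.

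**Events to expect.** Protocol section 17.2 lists events from earlier studies. Besides skin reactions these include headache, diarrhoea, fatigue, vomiting and "Nasopharyngitis". The cohort 2 follow-up call (protocol section 13.4) asks about side effects beyond the treated site.

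**Questionnaire.** The form in protocol Appendix B takes one tick per question. Question 3 asks "Overall, how satisfied were you with study medication", without reference to a side. SAP section 8.2.3.2 reports numbers of patients as a proportion of the treatment set, and question 5 as the proportion of patients who picked the active side correctly. The SAP Appendix 3 shell instead places every item, including "Overall, how satisfied were you with the study medication", under ACTIVE and PLACEBO with no overall column. For question 5 it has a percentage correct under each arm.

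**The concern.** A split-body design can compare arms for events at a treated site. It cannot do so for events that affect the whole patient, because each patient is in both arms at once. If the tumour is the only unit, the analyst has to decide, without guidance, where a systemic event goes: to no tumour, to one, or to all of that patient's tumours. The reported rate then depends on that decision. Copying one event to several tumours also makes it look like several independent observations in the confidence interval.

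AEs over the 12-week treatment period are a named secondary outcome of cohort 2, so the affected table is a planned result. The questionnaire shell has a related fault: it asks for two arm-specific answers where the form collects one. Question 5 matters most there, because protocol section 12 uses it to check the blind.

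**Working it through.** The plan gives no figure on this point. Its only design calculation concerns the response rate and is not in question. The check compares counting units and then illustrates what an unstated rule could do.

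**Step 1: which systemic events have a patient-level count under SAP section 7**

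| Systemic event | Patient-level count |
|---|---|
| Moderate or severe, treatment-related | Yes |
| Mild, treatment-related | No |
| Any severity, not judged related | No |

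The two rows marked No can enter a summary only through the tumour counts. Neither SAP section 7 nor the Appendix 2 shell says how.

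**Step 2: one systemic event in one patient**

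Inputs: 150 tumours in 15 to 20 patients (SAP 1.1), with 8 or 10 tumours per patient (protocol 7.2). Since 150/10 = 15 and 150/8 = 18.75, the two layouts are 15 patients × 10 = 150 tumours and 19 patients × 8 = 152 tumours. Assumption: exactly one patient has one such event. Intervals are exact binomial (Clopper-Pearson) 95%.

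| Where the event is placed | 15 patients × 10 | 19 patients × 8 |
|---|---|---|
| Counted per patient | 1/15 = 6.7% (0.2 to 31.9) | 1/19 = 5.3% (0.1 to 26.0) |
| No tumour | 0/150 | 0/152 |
| One tumour | 1/150 = 0.7% (0.0 to 3.7) | 1/152 = 0.7% (0.0 to 3.6) |
| All the patient's tumours | 10/150 = 6.7% (3.2 to 11.9) | 8/152 = 5.3% (2.3 to 10.1) |

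Against the nominal 150 tumours, copying adds 8/150 = 5.3% or 10/150 = 6.7%.

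**Step 3: why the copied interval is too narrow**

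In the 15 × 10 layout the point estimate is the same, 6.7%, but the interval is 11.9 − 3.2 = 8.7 points wide instead of 31.9 − 0.2 = 31.7. Copied events agree perfectly within a patient, so the intra-patient correlation is 1. The design effect is 1 + (10 − 1) × 1 = 10, and the effective sample is 150/10 = 15, the number of patients.

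**Step 4: what copying does to the arm comparison**

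Ten copied tumours split as 5/75 active and 5/75 placebo, so the arm difference changes by 5/75 − 5/75 = 0. It does change if the same patient also has local reactions. For example, a patient with reactions at all 5 active tumours and no placebo tumour contributes 5/75 against 0/75. After copying a headache, that becomes 5/75 against 5/75. Any masking is confined to such patients.

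**Step 5: how often this might arise**

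The non-skin events in protocol 17.2 sum to 5 + 3 + 3 + 2 + 2 + 2 + 2 + 1 + 1 = 21% (headache, nasopharyngitis, diarrhoea, rhinitis, upper respiratory infection, cough, back pain, fatigue, vomiting). If these were per-patient rates that carried over, 0.21 × 15 = 3.2 and 0.21 × 20 = 4.2 events. The protocol does not say whether the percentages are per patient or per event, and they come from other populations, so this shows only that such events are plausible.

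**Step 6: questionnaire**

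The form gives one answer per patient, and SAP 8.2.3.2 analyses one answer per patient. The Appendix 3 shell needs one answer per arm. The form and the text agree; the shell does not fit either.

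**The case against.** Tumour-level counting is the right unit for application-site reactions, which are the comparison this design was built to make. A reader might infer that systemic safety is lost altogether. The documents do not support that: SAP section 7 counts patients with moderate or severe related AEs once each and without an arm, descriptions may be listed, serious events follow their own reporting route (protocol 17.4), and the data monitoring committee reviews safety. In 15 to 20 patients a listing would show much of the rest. This stands, but the listing is optional, and a list has no denominator or interval.

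A reader might also infer that differences in local reactions will be hidden. That would require events to be copied to all tumours, which the SAP nowhere prescribes, and even then only patients with both kinds of event are affected (step 4). The figure of 5.3% to 6.7% rests on the same assumption.

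Finally, a reader who sees only Appendix 3 might conclude that the planned questionnaire analysis is wrong. It is not: the text of SAP 8.2.3.2 is correct, and the fault lies in the shell. The outcome is acceptability of the trial treatment, so nothing obliges the trial to ask about each jar separately. Doing so would alter a form in the protocol that patients complete.

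**Conclusion.** The point holds in a limited form. In Phase 2a, mild treatment-related systemic AEs, and systemic AEs of any severity not judged related, have no patient-level count, and no rule places them in the tumour table. One such event could be reported as anything from 0% to 6.7% of tumours. That range is illustrative: it assumes one event in one patient with 8 or 10 tumours, and the SAP itself prescribes none of the placements. Under full copying, the interval would be about a quarter as wide as the patient-level one (8.7 against 31.7 points). Moderate or severe related events are handled properly at patient level.

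The questionnaire issue is a contradiction between a correct text and a shell that cannot be filled as drawn. Neither issue touches the primary outcome. Both should be settled before the final analysis, because they decide what a named secondary safety outcome and the check of the blind will show.

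**What to change.** 1. In SAP section 7, split Phase 2a events by site. Report application-site AEs by tumour and side, active against placebo within patient, and let any interval on tumour counts allow for clustering within patients.
2. Report all other AEs per patient, at any severity and causality, with no arm column. Add per-patient rows for any AE and any treatment-related AE, and keep the existing moderate or severe related row.
3. State the attribution rule: an event not located at a treated site is assigned to no tumour and no arm.
4. Redraw the Appendix 2 AE shell to match.
5. In the Appendix 3 questionnaire shell, replace the ACTIVE and PLACEBO columns with one all-patients column, and show question 5 as correct, incorrect or don't know.

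The cost is a revision of the SAP 7 text and of two table shells. No patient form changes. It assumes that AE records show whether an event was at a treated site and at which tumour; the tumour-level counts already planned need the same information. The phrase in protocol 14.1 about proportions of tumours with AEs can stand, since the application-site table satisfies it.
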